# **Trial Protocol**

## **Background**

### **Study Purpose and Rationale:**

Hereditary breast and ovarian cancer syndrome (HBOC) is an inherited condition that is most commonly associated with mutations in the BRCA1 and BRCA2 genes. Mutation carriers have lifetime risks of breast and ovarian cancer of 40-60% and 20-40%, respectively. Risk management options include intensive breast cancer screening, risk-reducing surgeries, and chemoprevention, which have been shown to improve early detection and reduce cancer incidence and mortality. In particular, prophylactic bilateral salpingo-oophorectomy has been associated with a 60-77% reduction in all-cause mortality among BRCA mutation carriers. Based upon U.S. Preventive Services Task Force guidelines, an estimated 5% of women unaffected with breast cancer are eligible for genetic testing for HBOC, but only 14% of those eligible were referred and 4% had BRCA genetic testing. Many women may be unaware of their high-risk status due to our inability to adequately screen them in the primary care setting. Other reasons for low uptake include inadequate time for counseling and insufficient knowledge about risk-reducing strategies. Women from racial/ethnic minorities are less likely to seek genetic testing for HBOC, contributing to poorer clinical outcomes in these populations compared to non-Hispanic whites. Alternatively, decreasing inappropriate genetics referrals is also important for reducing anxiety and allowing genetic services to be used more efficiently. More research is needed to develop optimal strategies for engaging high-risk women in informed decision-making about genetic testing for HBOC.

The objective of this study is to expand genetic testing for HBOC to a broader population of high-risk women by prompting appropriate referrals from the primary care setting with the use of an electronic health record-embedded breast cancer risk navigation (BNAV) tool. To address patient-related barriers to genetic testing, we developed a web-based decision aid, RealRisks, which is designed to improve genetic testing knowledge, accuracy of breast cancer risk perceptions, and self-efficacy to engage in a collaborative dialogue about genetic testing.

Provide a description of how the confidentiality of study data will be ensured, addressing concerns or protections that specifically relate to the data storage elements identified above (e.g. hard copy, electronic, system, and/or endpoint): All subjects are assigned code numbers upon enrollment into the study. These codes are assigned to collected data and separated from a subject's name or any other information that could identify them. The research files that link a subject's name to the code number will be kept in locked file cabinets at the Department of Biomedical Informatics, and only the investigators and the study staff will have access to the files. All computer files will be protected by passwords available only to authorized study personnel. Electronic versions of consent forms and questionnaires will be administered by study staff and the data will be stored on our secure database server administered by the Department of Biomedical Informatics (system ID 5058), on the MC-domain shared drive administered by CUMC central IT (system ID 3959), and on a Filemaker database server administered through the Department of Medicine (system ID 4029). Paper versions of CRFs are also transferred to the Velos Clinical Study Manager (system ID 3945) provided by the HICCC. Digital versions of the

research files that link a subject's name to the code number are also kept in the certified systems referenced above. Only those individuals listed in the Personnel Section of this protocol will have access to these linking files. In addition, access to the BNAV tool for PCPs is through CUIT's Central Authentication Service (CAS), which uses the Columbia UNI. PCPs will only be able to see the health information of patients for whom they provide care.

### **Privacy and Security:**

Provide a description of how the confidentiality of study data will be ensured, addressing concerns or protections that specifically relate to the data storage elements identified above (e.g. hard copy, electronic, system, and/or endpoint):

All subjects are assigned code numbers upon enrollment into the study. These codes are assigned to collected data and separated from a subject's name or any other information that could identify them. The research files that link a subject's name to the code number will be kept in locked file cabinets at the Department of Biomedical Informatics, and only the investigators and

the study staff will have access to the files. All computer files will be protected by passwords available only to authorized study personnel. Electronic versions of consent forms and questionnaires will be administered by study staff and the data will be stored on our secure database server administered by the Department of Biomedical Informatics (system ID 5058), on the MC-domain shared drive administered by CUMC central IT (system ID 3959), and on a Filemaker database server administered through the Department of Medicine (system ID 4029). Paper versions of CRFs are also transferred to the Velos Clinical Study Manager (system ID 3945) provided by the HICCC. Digital versions of the research files that link a subject's name to the code number are also kept in the certified systems referenced above. Only those individuals listed in the Personnel Section of this protocol will have access to these linking files. In addition, access to the BNAV tool for PCPs is through CUIT's Central Authentication Service (CAS), which uses the Columbia UNI. PCPs will only be able to see the health information of patients for whom they provide care.

**Description of the protections in place to safeguard participants' privacy while information is being collected.**

For participants who are recruited in-person, they are approached and asked to participate in our study while they are at their primary care appointment at one of the clinic locations listed in the protocol. The discussion about the study and the informed consent process takes place inside of a private room that has been designated by the directors of each clinic.

Participants are asked survey questions directly by study staff while in the room or the participants are given the opportunity to fill out the surveys on their own either in the room or in the waiting area.

For participants who are recruited and complete study procedures over the phone, only staff who are listed in this protocol will have access to the study phone line and the study office. Research staff designated to collect consent will interact with participants over the phone in an office where 1-3 study personnel also sit.

**Procedures:**

Primary Care Providers (PCPs):

Potential PCP participants will be recruited from the CUMC/NYP Ambulatory Care Network (ACN) clinics and Columbia Doctors practices.

PCPs will be approached either in person, via mail, via email, or via phone. PCP recruitment flyers will also be posted at the clinics. The PCP's informed consent will be obtained by the research staff listed in the personnel section.

Eligibility criteria for PCPs include:

1) Primary care providers, such as attending physicians, residents, nurse practitioners, physician assistants, and midwives, who see patients at CUMC/NYP ACN clinics or a Columbia Doctors practice

2) Able to provide informed consent

After providing informed consent, PCP participants will complete a baseline questionnaire that collects information on their personal and professional characteristics, subjective risk communication confidence, confidence in managing patients with a family history of breast and ovarian cancer, knowledge, attitudes, orientation towards shared decision making, subjective norms, perceived behavioral control, and intention to refer high-risk patients to genetic testing. Primary care providers will be randomized to either the intervention or control arm.

PCPs in the intervention arm will then be given the Breast Cancer Risk Navigation Tool (BNAV), a web-based provider clinical decision support tool

(<https://kyras.dbmi.columbia.edu/bnav/>), and will be asked to interact with the tool prior to the next clinical encounter with their participating patients. Through BNAV, the PCP will be able to access a patient's individualized risk profile, including family pedigree, and an educational module on genetic testing. The PCP will also be sent a copy of their patient's risk assessment information (BNAV PCP Action Plan) through email and a secure health message (SHM). The BNAV website will include a list of participating patients who are randomized to receive the intervention. The PCP will also be able to view a BNAV notice within the electronic health record (EHR) in iNYP, which includes the patient's personalized breast cancer risk profile and family pedigree.

PCPs in the control arm will not have access to a populated BNAV patient table, nor will they receive an action plan. These PCPs will, however, be able to view the BNAV notice within the electronic health record (EHR) in iNYP, which includes their patient's personalized breast cancer risk profile. PCPs will be asked another survey 6 months after baseline. This survey will assess confidence in managing patients with a family history of breast and ovarian cancer, knowledge, attitudes, orientation towards shared decision making, subjective norms, perceived behavioral control, and intention to refer the patient to genetic testing.

PCPs will also be asked to complete a survey after clinic visits with patients who are also participating in the research study. This survey will assess shared decision making.

Patients:

Participating PCPs' patients will also be recruited and will be pre-screened using a breast cancer risk survey including the Six-Point Scale family history screener to determine eligibility for genetic testing. If found eligible for the study, patient participants will participate in an informed consent process.

Patients will also have the option of self-referring themselves to the pre-screener. If a patient is found eligible, and her provider is not already enrolled in the study, we will recruit this provider as well. We will identify these providers either through a patient's self-report or from the EHR. After completing the prescreener survey, if a patient is eligible, a research team member will administer the BEATRICE Family History Intake Form over the phone or in person. The data collected by this form will flush out the data collected in the prescreener and provide more

family history data that is needed for RealRisks to run its models. This information can also help us to verify that the patient is eligible.

Eligibility criteria for accrual of patient research participants into the cluster randomized controlled trial include:

- 1) Women, age 21-75 years without a personal history of breast or ovarian cancer
- 2) Meets criteria for genetic testing based upon the Six-Point Scale, defined in this study as 4 points or higher
- 3) No prior genetic counseling or testing for hereditary breast and ovarian cancer (HBOC)
- 4) Sees a primary care provider in the Columbia University/New York Presbyterian Hospital Ambulatory Care Network (ACN) or a Columbia Doctors practice
- 5) Understands as is willing to provide informed consent in English or in Spanish

Patient participants who enroll and complete the pre-screening questions will receive a risk notification indicating whether they are eligible for BRCA genetic testing. This risk message will be given to the participant either in-person, through mail, or by email.

Once patients have consented, we will check if they are registered to the clinic's Patient Portal. If not, we will work to register patient participants for the portal using the phone, email, in-person assistance, email invitations, and existing patient portal resources.

Upon meeting eligibility criteria and providing consent, all patient participants will be asked to complete the Baseline Survey. The baseline questionnaire assesses perceived risk and breast cancer worry, interest in genetic testing, health and eHealth literacy, decision self-efficacy, subjective numeracy, acculturation, preparation in shared decision making, decision conflict, knowledge, and attitudes by using validated and adapted measures. The baseline questionnaire is estimated to take 15-20 minutes and will be done either on paper, online, or over the phone. Patient participants will then receive an educational brochure for the CUMC Clinical Breast Cancer Prevention Program and a brochure that provides education on genetics and breast cancer. The risk notification and brochures will serve as the educational materials for the intervention and control arms. Those who do not meet high-risk criteria will be reassured that genetics referral is not indicated at this time, but should be reassessed if their personal or family history of cancer changes.

After completing the baseline questionnaire, patients in the intervention arm will also receive a link to the RealRisks decision tool. The research staff will determine the date and time of the patient's next PCP appointment from the scheduling systems, the EHR, or the patient's self-report. Patients will be encouraged to use the tool within 2 weeks prior to their PCP visits and genetic counseling visits. Patients will be encouraged to bring a print-out of their action plan (which will also be available to the PCP in the BNAV toolbox) based upon their interactions with the RealRisks decision aid, in order to facilitate discussions about genetic counseling and genetic testing. Control patients will be given access to and asked to complete RealRisks after they have completed all other study milestones and surveys.

All patients will be followed-up to complete a second survey within two months after they are given RealRisks and/or the control educational material. This survey assesses breast cancer worry, breast cancer risk perception, decision self-efficacy, knowledge, attitudes, preparation in decision making, decision conflict, and genetic testing decisions and asks for feedback on the

intervention and/or control materials. The survey will be done either on paper, online, or over the phone. One week prior to an intervention-patient's scheduled clinic visit with her enrolled-health care provider, she will be sent a prompt that will remind her of the information she entered into RealRisks and help her prepare for her appointment.

A survey will also be administered after a participant's next scheduled appointment with her primary care provider. This survey will assess perceived risk and breast cancer worry, knowledge, attitudes, decision conflict, genetic testing decisions, shared decision making, trust in health care providers, and decisional regret. This survey will be distributed either on paper, online or over the phone. The clinic visit to which this survey refers will be the patient's first visit after one month has passed since the patient was sent the high-risk letter/brochure/educational materials. If the patient is able to finish all preceding study milestones (baseline, RealRisks if in the intervention arm, and the 1-month survey) and then she has a clinic appointment before the one-month time point, this clinic visit can count. Additionally, if the patient missed or had to cancel the first visit after one month, we will use the next scheduled visit. If the patient and provider decide to speak more informally, for example over the phone, instead of hold a formal visit to discuss genetic counseling referral, we will count this as a visit.

Six months after patients are given RealRisks and/or the control materials, we will administer another follow-up survey. This survey will assess perceived risk and breast cancer worry, knowledge, attitudes, decision self-efficacy, decision conflict, genetic testing decisions, decisional regret, and genetic testing uptake. This survey will be distributed either on paper, online, or over the phone.

We will also assess for appropriate referrals to and uptake of genetic counseling and genetic testing after 6 months by using data from the EHR and scheduling systems.

To keep patient participants engaged throughout the research study, we may send calendars, thank-you cards, birthday cards, appointment reminders, and other similar retention materials. Providers will be sent post-it notes, thank-you cards, and other similar retention materials.

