**Reimbursement/compensation:**

The patient participant will receive \$25 for the baseline survey, \$25 for the two-week survey, \$50 for the six-month survey, and \$50 for the survey after the next clinical appointment with their primary care provider. Patient participants will also receive \$20 for completing the RealRisks decision aid and \$5 for scheduling an appointment with their enrolled health care provider.

The provider participant will receive \$50 for the baseline survey, \$50 for the second survey, and \$50 for each post-encounter survey.

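### The second patient survey carries three different timings, and the early-visit rule for the post-visit survey depends on arm and on RealRisks completion

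*Protocol*

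**What the plan says.** The Patients part of the protocol's Procedures section describes four patient surveys: baseline, a second survey, a post-visit survey and a six-month survey. Three places bear on when the second one is taken.

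- Procedures, on the second survey itself: "All patients will be followed-up to complete a second survey within two months after they are given RealRisks and/or the control educational material".
- Procedures, in the rule for the post-visit survey, where the steps before the visit are listed as "baseline, RealRisks if in the intervention arm, and the 1-month survey".
- Reimbursement/compensation, which pays for four patient surveys, one of them described by the words "for the two-week survey".

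On use of the decision aid, Procedures says: "Patients will be encouraged to use the tool within 2 weeks prior to their PCP visits".

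The post-visit survey refers to an index visit. By default this is the "first visit after one month has passed since the patient was sent the high-risk letter/brochure/educational materials", with no condition on arm. The exception begins "If the patient is able to finish all preceding study milestones (baseline, RealRisks if in the intervention arm, and the 1-month survey" and continues, after the bracket, "and then she has a clinic appointment before the one-month time point, this clinic visit can count".

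**The concern.** There are two separate faults.

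First, staff cannot tell from the protocol when the second survey is due. It collects decision conflict, knowledge and attitudes, which bear on Aim 2 (Research Aims & Abstracts). Depending on which section is followed, an intervention woman may answer before she has used RealRisks, after she has used it, or after she has already seen her provider. The score means something different in each case.

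Second, the early-visit exception sets a condition after randomisation that exists in one arm only. In the intervention arm, early index visits can come only from women who completed RealRisks. In the control arm, nothing comparable selects them. Among the patient follow-up surveys, shared decision-making is listed only in the post-visit survey, so that outcome has no other follow-up measurement from patients to fall back on.

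**Working it through.** The protocol states no figure on this point. Its only power statement concerns the primary endpoint and does not enter. The check is a comparison of passages, followed by an illustration under stated assumptions.

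**Do the three labels mean the same survey?** Procedures describes four patient surveys and Reimbursement/compensation pays for four. Baseline, six-month and post-appointment match directly. The remaining payment, for two weeks, must be the second survey. The one-month label sits among the steps that precede the post-visit survey, after baseline, so it too can only be the second survey.

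**How far apart are the timings?** Two weeks is day 14, one month about day 30, and two months up to about day 60. The ratio of last to first is 60/14, about 4.3. None of the three differs by arm.

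**What does each timing do to the measurement?** Take the earliest default index visit, about day 31. The encouraged RealRisks period opens at 31 − 14 = day 17.

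- Survey at day 14: a woman following that advice for this visit answers 3 days before the period opens. Later visits widen the gap.
- Survey at about day 30: for the day-31 visit, it falls inside the period of use and before the visit.
- Survey up to about day 60: it can follow any index visit from day 31 onward.

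**How does this interact with the exception?** The second survey must be finished before an early visit can count. If it is due at day 14, about 30 − 14 = 16 days remain in which a qualifying visit can fall. If it is due at about day 30, almost none remain. The unresolved survey date therefore governs how often the arm-dependent rule operates.

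**How large could the arm difference be?** The following inputs are assumptions; the protocol gives none of them.

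- v: share of women with a visit before one month, 10% to 50%.
- s: share of those who have finished baseline and the second survey by then, 50% to 80%.
- r: share of those in the intervention arm who have also completed RealRisks, 50% to 100%.

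With v and s equal in the two arms, the share of women with an early index visit is v × s in control and v × s × r in intervention. The difference is v × s × (1 − r).

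| v | s | r | Control | Intervention | Difference (points) |
|---|---|---|---|---|---|
| 10% | 50% | 90% | 5.0% | 4.5% | 0.5 |
| 30% | 80% | 70% | 24.0% | 16.8% | 7.2 |
| 50% | 80% | 50% | 40.0% | 20.0% | 20.0 |

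At r = 100% the difference is 0. Over the assumed ranges it runs from 0 to 20 percentage points. The direction is fixed as long as v and s are equal between arms: fewer early index visits in the intervention arm, all of them from RealRisks completers.

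**The case against.** The strongest reply is that only one of the three timings is scheduling text. The two-month wording is an outer limit, and a survey at two weeks or at one month falls inside it. The other two are names, one in a parenthesis and one in a payment list. The milestone list also puts RealRisks before the survey, and the survey asks for feedback on the materials, so it is evidently meant to follow use. A woman surveyed before use is then a matter of non-adherence, which dilutes a comparison by assigned arm without biasing its timing.

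Part of this stands. The timings apply to all patients, so they create no arm difference in scheduled timing. The intended order is probably use first, survey second. But two weeks and one month cannot both be the target, and the advice to use RealRisks shortly before the visit works against that order when the survey comes early. A woman who follows the advice exactly can still be surveyed before use, so this is not only non-adherence.

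On the exception, the reply is that it is narrow. It needs all milestones finished and a visit before one month; every other woman follows the common default. A woman who fails it is not excluded, since a later visit is used. This stands as a limit on size, and the range above includes zero. It does not remove the asymmetry, because the condition is written into the rule.

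A reader might infer that Aim 2 as a whole is measured at different times in the two arms. The protocol does not support that. The six-month survey has the same wording for both arms and repeats decision conflict, knowledge and attitudes. The arm-dependent rule reaches only the post-visit survey, and only women with a visit before one month.

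**Conclusion.** The concern holds in limited form, and both parts should be corrected.

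- The second survey's timing is inconsistent across Procedures and Reimbursement/compensation. This leaves the meaning of its decision-conflict score open but does not by itself separate the arms.
- The early-visit exception selects the index visit by arm and by adherence. Post-visit measures, above all shared decision-making, may therefore refer to differently selected visits in the two arms.

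The protocol does not allow the size to be derived. The 0 to 20 points are illustrative, and they describe how many index visits are early, not bias in any score. A reader might also want to state how much the decision-conflict effect is diluted. If a share q is surveyed before use and there is no effect before use, (1 − q) of the effect remains, for example 70% at q = 30%. Neither q nor the zero effect has a source in the protocol, so this is no finding about the trial.

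The primary endpoint, counseling uptake by 6 months from EHR and scheduling data, does not depend on either rule. No sample-size figure changes.

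**What to change.** 1. Give the second survey one target date and window, and use it in both places in Procedures and in Reimbursement/compensation. Count it in both arms from the date on which the risk notification and brochures are sent.
2. Define the index visit by one rule that is the same in both arms and does not depend on RealRisks completion. The simplest is to keep the existing default, the first PCP contact after one month from that same date, and delete the early-visit exception.

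The cost is wording in three places. A few early visits will no longer count. For those women the post-visit survey may refer to a later contact, possibly after the referral discussion has taken place, but by the same rule in both arms. A fixed survey date will not guarantee that every intervention woman has used RealRisks by then, since use is tied to the visit. It does make the assessment time known and common to both arms.
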